#### Subject-level analysis

Although the data for the primary outcome itself may not be normally distributed [11], making use of the central limit theorem with the relatively large sample size that will be recruited in this research, the distribution of the mean would be normal. Non-inferiority of the 25 % AgNO_3_ solution followed by 5 % NaF varnish to 38 % SDF solution can be claimed if the lower limit of the confidence interval for the difference in the mean number of arrested surfaces is greater than the non-inferiority margin of −0.5. This test for non-inferiority will only be performed for the primary endpoint, the number of arrested surfaces after 30 months. Furthermore, a Student’s *T* test will be performed to study the effects of the treatment on the number of arrested caries surfaces at the 18-month examination. This research will also study the effect modification. The variables that are considered to possibly modify the treatment effects on the outcome variable include the patient’s gender, baseline caries experiences, treatment group assignment, oral hygiene habits, fluoride agent use, parent-assisted tooth-brushing, dental visit behaviour, snacking habits, parental educational level, total family income, and family status (single-parent or two-parent households).

Besides the primary outcome, Student’s *T* tests will be also used to test the between-group differences regarding the number of new caries surfaces, increment in the number of non-vital teeth, and number of hyper-mobile teeth across the follow-up examinations.

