### Clinical examination

A clinical examination of the participating children will be performed in the kindergarten, primarily through a careful visual inspection with the aid of a disposable World Health Organisation Community Periodontal Index (CPI) probe (405/WHO probe, Otto Leibinger, Mühlheim, Germany) and a front-surface dental mirror with light-emitting diode intra-oral illumination (MirrorLite, Kudos Crown Limited, Hong Kong, China). The oral hygiene status will be measured using the visible plaque index (VPI). The buccal and lingual surfaces of 6 index teeth (55, 51, 63, 71, 75, and 83) will be examined. The presence or absence of visible plaque on the caries surface will also be recorded.

The tooth status (decayed, missing, filled surfaces (dmfs) score), tooth discolouration, and hyper-mobility will be recorded. Teeth with a caries lesion extending into the pulp or signs suggesting that the teeth are non-vital, such as tooth discolouration, hyper-mobility or abscess, will not be included in this study.

The caries will be diagnosed at the cavitation level. The carious lesion will be gently explored with the CPI probe in the centre of the lesion. Great care will be taken to avoid tooth damage during the probing. A lesion will be recorded as active if softness is detected upon gentle probing. If the dentine surface is hard to probing, it will be classified as an arrested caries [11–13, 15, 27]. All surfaces (i.e., buccal, lingual, mesial, distal, and occlusal for posterior teeth) of each tooth will be assessed. Active caries at the baseline that become arrested in the follow-up examinations will be used as the main treatment outcome.

A designated experienced outreach dentist will be the examiner throughout the 30-month study. The intra-examiner agreement on the plaque and caries assessment will be monitored and conducted in 10 % of the children at each stage of the study.

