### Randomisation and treatment allocation

#### Allocation concealment

The participating children with caries will first be categorised as either: (1) having a high caries rate (or severe early childhood caries, as defined by the American Academy of Paediatric Dentistry [1]), which is defined as the presence of more than 3 untreated caries surfaces, or (2) having a low caries rate. The children will then be allocated by a stratified randomisation method using a computer-generated random-number table into the following 2 groups:Group A – biannual topical application of 25 % AgNO_3_ solution followed by 5 % NaF varnish; andGroup B – biannual topical application of 38 % SDF solution followed by a placebo varnish.

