### Sample size and power calculation

This non-inferiority trial aims to measure the anti-caries efficacy of a 25 % AgNO_3_ solution followed by 5 % NaF varnish versus a 38 % SDF solution with a non-inferiority margin of −0.5 for the difference in mean number of arrested caries surfaces, which is considered clinically negligible (corresponding to an effect size = 0.25, assuming a standard deviation of 2.5 and true difference of 0) [11]. The estimated sample size, calculated with the help of a statistician, is based on the lower limit of the 2-sided 95 % confidence interval for the difference being set above the non-inferiority margin (−0.5), and statistical power of the study being set at 90 % (*β* = 0.10). The total required number of preschool children with caries will be 856 calculated with the use of statistical power analyses software, G*Power (version 3.1.7; Franz Faul, Universität Kiel, Kiel, Germany). Anticipating the caries prevalence to be 35 % [28] and the overall 30-month drop-out rate to be 20 % [11], the initial sample size for screening should thus be 3058 with a total of 1070 kindergarten children being recruited in the 2 study groups at the baseline examination.

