### Statistical methods

A data management and statistical analysis protocol has been developed for the clinical trial. This details the procedures for data entry, management and cleaning, and data analysis.

The collected data will be entered into an Excel file (Microsoft Corp., Redmond, WA, USA) by two persons, and the data will be compared to minimise data entry errors. The intra-examiner agreement in caries diagnoses will be assessed by Cohen’s Kappa statistics. The level of statistical significance for all 2-sided tests will be set at 0.05. For the 1-sided tests, the level of statistical significance will be set at 0.025.

An intention-to-treat analysis will be performed in this study. We expect that the drop-out rates of the two groups will be similar because the treatment protocols and treatment outcomes (arrested caries with blackening of the lesion) are the same. If the number of children who strayed from the protocol (for instance, by not adhering to the prescribed 6-month intervention, or by being withdrawn from active treatment) are different between the 2 groups, a per-protocol analysis will be performed. In that case, only the patients who complete the entire clinical trial according to the protocol will be counted towards the final results.

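### The 30-month non-inferiority interval, as described, uses neither the baseline active-surface count nor the randomisation stratum, so it is valid but wider than it need be

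*Protocol article*

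**What the plan says.** The decision rule is in the protocol article under Subject-level analysis: AgNO3/NaF may be called non-inferior when the "lower limit of the confidence interval for the difference in the mean number of arrested surfaces is greater than the non-inferiority margin", which is −0.5. The section supports this by appeal to the central limit theorem, given that the counts may not be normal. It names no stratum and no covariate for this interval. The same outcome at 18 months, and the secondary counts, are assigned Student's t tests. Baseline caries experience appears only in a list of possible effect modifiers, there and in the Discussion.

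Three other sections bear on the point:

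- **Clinical examination.** "Active caries at the baseline that become arrested in the follow-up examinations will be used as the main treatment outcome". The Outcome measure section repeats this as a per-child count at 30 months. Lesion activity is recorded at baseline by probing.
- **Allocation concealment.** Children are classed as high or low caries rate, with the cut at more than 3 untreated caries surfaces. "The children will then be allocated by a stratified randomisation method using a computer-generated random-number table".
- **Sample size and power calculation.** The trial is sized "with a non-inferiority margin of −0.5 for the difference in mean number of arrested caries surfaces", "corresponding to an effect size = 0.25, assuming a standard deviation of 2.5 and true difference of 0", and the calculation is "based on the lower limit of the 2-sided 95 % confidence interval for the difference being set above the non-inferiority margin", with "statistical power of the study being set at 90" %. It asks for 856 evaluable children.

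**The concern.** Only surfaces active at baseline can become arrested, so each child's baseline active count is an arithmetic ceiling on that child's outcome. A child with one active surface can score 0 or 1, and a child with ten can score anything up to 10. Part of the spread in the outcome therefore reflects how many lesions children started with, which treatment cannot affect. The investigators stratify on caries burden, so they already regard it as important.

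A raw difference in means leaves all of that spread in the standard error. A model that includes the baseline count and the stratum removes the part they explain and still estimates the same mean difference. What is at stake is precision: a wider interval makes it more likely that a treatment that truly is non-inferior fails to clear −0.5.

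**Working it through.** **Inputs from the protocol.** Margin −0.5, SD 2.5, true difference 0, 2-sided 95 % interval (one-sided 0.025, consistent with Statistical methods: "For the 1-sided tests, the level of statistical significance will be set at 0.025"), and 856 evaluable children. Equal allocation is assumed because the ratio is not stated, which gives 856/2 = 428 per arm.

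**Step 1: the plan's own figure.** The standardised margin is 0.5/2.5 = 0.20. For two unadjusted means, n per arm = 2 × ((z_α + z_β)/0.20)².

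- One-sided 0.025, power 90 %: 2 × ((1.9600 + 1.2816)/0.20)² ≈ 525.4, so 526 per arm and 1052 in total. This is not 856.
- One-sided 0.05, power 90 %: 2 × ((1.6449 + 1.2816)/0.20)² ≈ 428.2 per arm, and 2 × 428 = 856.

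For the present point, this shows that the sizing is a two-sample comparison using the full outcome SD, with no allowance for covariates. The mismatch between 856 and the stated 90 % power, and between 0.20 and the printed effect size of 0.25, is a separate matter.

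**Step 2: unadjusted precision at 428 per arm.** SE = 2.5 × √(2/428) = 0.171. The half-width is 1.96 × 0.171 = 0.335. Power = Φ(0.5/0.171 − 1.96) ≈ 83.3 %.

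**Step 3: precision after adjustment.** If the baseline active count has correlation r with the arrested count, the residual SD is 2.5 × √(1 − r²) and the interval narrows by 1 − √(1 − r²). The protocol does not give r, so it is varied:

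| r (assumed) | Residual SD | Half-width | Narrower by | Power at 428 per arm |
|---|---|---|---|---|
| 0 | 2.500 | 0.335 | 0 % | 83.3 % |
| 0.3 | 2.385 | 0.320 | 4.6 % | 86.6 % |
| 0.5 | 2.165 | 0.290 | 13.4 % | 92.2 % |
| 0.7 | 1.785 | 0.239 | 28.6 % | 98.4 % |

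**Step 4: is a useful r plausible?** Suppose each of N baseline active surfaces arrests with probability p, with within-child correlation ρ and with p unrelated to N. Let m and V be the mean and variance of N. Then Var(Y) = p²V + p(1 − p)[m + ρ(V + m² − m)] and r² = p²V/Var(Y). Var(Y) is held at 2.5² = 6.25. The assumed ranges are m = 3 to 6, p = 0.5 to 0.8 and ρ = 0 to 0.4.

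- Lowest r (m = 6, p = 0.5, ρ = 0.4): V = (6.25 − 0.25 × 18)/0.35 = 5.0, so r² = 0.25 × 5.0/6.25 = 0.20 and r ≈ 0.45. The interval is about 11 % narrower.
- Highest r (m = 3, p = 0.8, ρ = 0): V = (6.25 − 0.16 × 3)/0.64 = 9.02, so r² ≈ 0.92 and r ≈ 0.96.

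None of m, p and ρ is in the protocol. If children with many lesions arrest a smaller share of them, r could be lower than this range.

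**The case against.** **Unadjusted is an inference.** The decision rule does not name the estimator for the 30-month comparison, and an adjusted mean difference would satisfy it as written. The t tests are assigned to the 18-month and secondary comparisons. The Statistical methods section mentions a separate analysis protocol that is not shown, and covariates are often listed in such a document. This stands as a limit on how firmly the point can be put. It does not remove it, because the article itself fixes the decision rule and its justification, and both, together with the sizing, describe a raw two-group comparison.

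**Nothing here is invalid.** A reader might infer that chance imbalance in lesion numbers contaminates the treatment difference on top of the stated uncertainty. The documents do not support that: under randomisation the raw difference is unbiased, and such imbalance is already inside the unadjusted SE of 0.171.

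**The standard error is not shown to be wrong.** A reader might also infer that analysing without the stratum makes the SE too large. That needs balance to be enforced within strata, for example by blocking. The protocol mentions only stratification and a random-number table. If balance is enforced, the unadjusted interval is conservative; if not, it is essentially correct.

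**The size is assumed, and the two variables differ.** The stratum counts untreated caries surfaces, while the ceiling is set by active surfaces on eligible teeth. The gain from one cannot be read off the other. This stands, and it is a reason to include both.

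**Conclusion.** The point holds as one of efficiency. The primary comparison, as described, does not use a baseline count that caps the outcome or the factor that stratified the randomisation, so the interval is wider than necessary. Its coverage is correct, or conservative if allocation is balanced within strata.

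The direction is secure provided that baseline count is prognostic, which the ceiling makes very likely. The size is not secure. Over assumed correlations of 0.3 to 0.7, the interval narrows by about 5 % to 29 %, and power at 428 per arm rises from about 83 % to between 87 % and 98 %.

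It would be tempting to present adjustment as the cure for the shortfall from 90 % to 83 %. The arithmetic would allow it if r is about 0.43 or more, since √(1 − 428/525.4) ≈ 0.43, but the protocol gives no value of r. The shortfall comes from the sample size calculation and needs its own correction.

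**What to change.** State the primary analysis as a linear model of the 30-month arrested count on treatment, baseline number of active surfaces and randomisation stratum, with robust standard errors because the spread of the outcome is likely to grow with the baseline count. Compare the adjusted mean difference and its 2-sided 95 % interval with the same −0.5 margin. Keep the unadjusted difference as a sensitivity analysis.

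Fix this before outcome data are seen by group. It matters here because the Ethical considerations section has unblinded team members reviewing examination data continuously, so a covariate choice made later would be open to challenge. If the separate analysis protocol already specifies such a model, one sentence under Subject-level analysis would bring the two into line.

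The cost is wording only. The variables are already collected, and the margin and the quantity estimated do not change.

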#### Surface-level analysis

To compare the differences in the time to caries arrest between the two treatment groups at the tooth surface level, a survival analysis will be adopted for the interval-censored data (because the time to arrest cannot be observed exactly but falls in the interval between the two examinations); this analysis will account for the possible correlation (clustering) between the observations of multiple surfaces from the same child. The statistical software SAS 9.2 for Windows (SAS Institute Inc., Cary, NC, USA) will be used for the analyses above.

### Ethical considerations

Ethics approval was obtained from the Institutional Review Board of the University of Hong Kong/Hospital Authority Hong Kong West Cluster (HKU/HAHKW IRB) (IRB reference number: UW 13–569). Informed consent will be sought from parents of each participating child prior to participation in the trial. In general, the trial will pose minimal risks to the participating children. In order to minimise risk, careful training has been provided to the field workers. A monitoring system is in place for potential adverse and serious adverse events, with a protocol for the management of these events and reporting at appropriate times to the HKU/HAHKW IRB.

All data from the baseline and follow-up examinations will be reviewed on a continuous basis by unblinded members ([name] and [name]) of the team to check on quality. The trial statisticians ([name] and [name]) will be asked to review the data at key points during the life of the trial. Reports will be submitted to the HKU/HAHKW IRB every 6 months for external quality control. All serious adverse events will be reported to the HKU/HAHKW IRB within 48 hours of being reported to the trial team.

## Discussion

This study is a non-inferiority clinical trial aiming to investigate whether biannual topical application of 25 % AgNO_3_ solution followed by 5 % NaF varnish is at least not appreciably worse than 38 % SDF solution in arresting caries in the primary teeth of children. The estimated sample size is based, with the help of a statistician, on the lower limit of the 2-sided 95 % confidence interval for the difference being set above the non-inferiority margin (−0.5) and statistical power of the study being set at 90 % (*β* = 0.10). As no other similar non-inferiority clinical trial has been conducted in this area, the non-inferiority margin of this trial cannot be inferred from previous studies. Since the number of dental caries surfaces is the integer and the hypothesis of this study is that 25 % AgNO_3_ solution followed by 5 % NaF varnish is at least not appreciably worse than 38 % SDF solution in arresting caries, the difference between the results (the number of caries arrested surfaces) is estimated to be between −1 to 0 (Group A minus Group B). After discussing with several experienced statisticians, we finally determined the non-inferiority margin of this study to be −0.5, which is the middle value between −1 and 0.

The evaluation will be conducted at 18-month and 30-month follow-up. Non-inferiority testing will only be performed for the primary endpoint, the number of arrested surfaces after 30 months. Additionally, a Student’s *T* test will be performed to study the effects of the treatment on the number of arrested caries surfaces at the 18-month examination. As different variables might provide different levels of influence on outcome variables, this research will also study the effect modification. The variables that are considered to possibly modify the treatment effects on the outcome variable include the patient’s gender, baseline caries experiences, treatment group assignment, oral hygiene habits, fluoride agent use, parent-assisted tooth-brushing, dental visit behaviour, snacking habits, parental educational level, total family income, and family status (single-parent or two-parent households).

We expect that topical application of 25 % AgNO_3_ solution followed by 5 % NaF varnish and of 38 % SDF solution can both effectively arrest ECC. The results of this study will add to the clinical trial information on the use of AgNO_3_ and NaF and will help to determine whether 25 % AgNO_3_ solution and 5 % NaF varnish are as effective as 38 % SDF solution in arresting childhood caries. Lower concentrations of silver and fluoride are contained in 25 % AgNO_3_ solution and 5 % NaF varnish, respectively, than in 38 % SDF solution; therefore, 25 % AgNO_3_ solution and 5 % NaF varnish are more favourable for use in young children. Because its use for caries management is painless, simple, low-cost, and approved in many countries, 25 % AgNO_3_/5 % NaF could be widely recommended and promoted as an alternative treatment to conventional invasive caries management, particularly among child patients who are too young for conventional dental care.

## Trial status

This randomised clinical trial has been registered in *ClinicalTrials.gov (U.S.)* under the registration number NCT02019160 on 11 December 2013. The recruitment of participating kindergarten children and their parents is in progress from 15 September 2014.

## Abbreviations

AgNO_3_: silver nitrate
CPI: Community Periodontal Index
dmfs: decayed, missing, filled surfaces score
ECC: early childhood caries
FDI: World Dental Federation
HKU/HAHKW IRB: The Institutional Review Board of the University of Hong Kong/Hospital Authority Hong Kong West Cluster
NaF: sodium fluoride
SDF: silver diamine fluoride
US: United States
VPI: visible plaque index
